### Study duration

The study intervention will take place during the entire ICU stay as well as during potential readmissions to the ICU. Therefore, the study duration will be variable for each patient. After ICU discharge both groups will receive the usual physiotherapy treatment and, if necessary, rehabilitation. Likewise, there will be no difference for participants of both groups in terms of medical attention, treatment and care during the whole study duration. The study will finish with a follow-up 6 months after hospital discharge.

### Outcome

The primary outcome measures are functional capacity using the 6-Minute Walk Test (6MWT) [35] and the ability to perform activities of daily living using the Functional Independence Measure (FIM) [36]; both will be evaluated at hospital discharge.

The secondary outcome measures were chosen to reflect the physical impairment after ICUAW and whether these important clinical outcomes can be improved by early training. They are as follows:

Muscle strength and ICUAW diagnosis at ICU discharge: Medical Research Council sum score [5, 37], handgrip strength using the JAMAR dynamometer (Sammons Preston Rolyan, Bolingbrook, IL, USA) [37, 38] and quadriceps muscle strength using a handheld dynamometer (Microfet 2, Biometrics, Almere, Netherlands) [38]. Muscle strength tests will only be performed if a patient can follow three out of five simple commands in order to assess their ability to cooperate as well as the level of consciousness beforehand [39].

Joint contractures, which are defined as limitations in range of motion, will be recorded after ICU discharge for the following joints: shoulder flexion, elbow flexion and extension, fist closure, hip flexion, knee flexion and extension and foot dorsiflexion [40].

Functional mobility will be measured with the Timed ‘Up & Go’ Test [41] at hospital discharge.

The quality of life 6 months after hospital discharge will be assessed with the Short Form 36 (SF-36, version 1.3) [42].

The overall time on mechanical ventilation, length of stay in the ICU and the hospital, as well as achieved milestones during the ICU stay (sitting on the side of the bed, sitting in a chair, standing or walking) will be reported.

Furthermore, the safety of early training, particularly the physiological response of the participants, any occurring AE, SAE and other complications related to bed rest as well as the feasibility, frequency, duration and content of the therapy, will be collected and analysed.

The schedule for the outcome assessments is shown in Table 1.

**Table 1 Tab1:** Schedule for enrolment, data collection, interventions and outcome measures

	Enrolment	Allocation	Post allocation			
Timepoint	ICU admission		ICU stay (daily)	ICU discharge	Hospital discharge	6-month follow-up
Enrolment:						
Eligibility screen	x					
Consent by nonparticipating doctor	x					
Allocation		x				
Informed consent by proxy		≤72 h				
Data collection:						
Demographic and diagnostic data		x				
APACHE II score	x					
SOFA score			x			
TISS 28 and 76	x			x		
Laboratory findings	x	x		x		
Medication			x			
Physiotherapy Interventions:						
Frequency, duration and content			x			
Safety and physiological parameters			x			
Mobility milestones			x			
Bed rest complications			x			
Serious/adverse events			x			
Outcome measures:						
Muscle strength: MRC sum score, handgrip and quadriceps strength				x		
Range of motion				x		
Functional Independence Measure				x	x	
Length of stay (ICU and hospital), days on mechanical ventilation					x	
6-Minute Walk Test					x	
Timed ‘Up & Go’ Test					x	
Short Form 36						x

*APACHE* Acute Physiology and Chronic Health Evaluation, *ICU* intensive care unit, *MRC* Medical Research Council, *SOFA* Sequential Organ Failure Assessment score, *TISS* Therapeutic Intervention Scoring System

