### Hypotheses

The primary hypothesis is that critically ill, mechanically ventilated adults who participate in an early endurance and resistance training, combined with early mobilisation, have an improved functional capacity and are, therefore, more functionally independent at hospital discharge compared to patients receiving the usual physiotherapy care. Secondary hypotheses are that this early training is as feasible and as safe as standard therapy. Further, we expect improvements in muscle strength at ICU discharge, fewer joint contractures, less time on mechanical ventilation, a shorter length of stay in the ICU and the hospital, and a higher quality of life at 6 months after hospital discharge compared to patients receiving usual care.

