### Safety

To ensure the patient’s safety all vital parameters, particularly heart rate, invasive blood pressure and oxygen saturation, will be continuously monitored and recorded by our Patient Data Management System (PDMS), which is routinely checked by the ICU staff. Furthermore, oxygen consumption, energy expenditure and the respiratory quotient by indirect calorimetry will be obtained 30 min prior to, during and for 15 min after physiotherapy. All adverse events (AE) will be noted. These are defined as any event that occurs during or up to 15 min after physiotherapy and persists despite an intervention or therapy interruption. It includes new haemodynamically relevant arrhythmias or otherwise unstable haemodynamics, oxygenation desaturation under 85 %, a fall or other injury as well as any accidental removals of a tube, catheter or similar devices. We use a qualitative physiological approach instead of strict target numbers, as optimal physiological goals for individual patients vary highly and depend on the underlying clinical condition [32]. If a participant exceeds or fails to exceed his individually set limits, the therapist will discontinue the session for the day and will record the reason. If this happens repeatedly, the principal investigator will withdraw the patient from the study. Serious adverse events (SAE) are defined as death, a life-threatening injury or an extension of the length of hospital stay. All SAEs and AEs will be recorded and reported to the principal investigator, who judges their severity and whether they were study-related. All SAEs will also be reported to the local ethics committee. Finally, all occurring complications related to bed rest, such as atelectasis, pneumonia, decubitus ulcer, thrombosis, contracture, delirium and a confirmed critical illness, polyneuropathy or myopathy, will be judged and recorded daily by the treating physician according to our current standard of care.

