### Statistical analysis

Study data will be analysed as randomised with SPSS (IBM SPSS Statistics Version 21) by both intention-to-treat (main analysis) and per-protocol analysis. However, the intention-to-treat analysis will only include participants with an informed consent, as adjusted in the sample size calculation. The level of significance will be set at *p* < 0.05. Descriptive statistics will be used to describe mean outcomes and distribution. Subsequently, the outcome parameters between the two groups will be compared using Student’s *t* tests for normally distributed data and the Mann-Whitney *U* test for nonnormal distribution. For repetitive data repeated measures analysis of variance (ANOVA) will be deployed and for correlations between variables the Spearman correlation coefficients or similar will be used. If missing data are more than 5 %, multiple imputations will be performed. There will be one planned interim analysis after enrolment of 35 patients for assessment of safety.

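### Ventilation time and length of stay are compared with no rule for death, so an arm with more early deaths can look better if mortality differs between the arms

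*Protocol article*

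**What the plan says.** - **Direction of benefit.** Hypotheses expects, in the trained arm, "less time on mechanical ventilation, a shorter length of stay in the ICU and the hospital".
- **Measure.** Outcome lists "The overall time on mechanical ventilation, length of stay in the ICU and the hospital" as quantities to be reported. Table 1 files "Length of stay (ICU and hospital), days on mechanical ventilation" under outcome measures, in the hospital discharge column only. There is no ventilator-free-day definition, no restriction to survivors and no value assigned to a death.
- **Test.** Statistical analysis says that "the outcome parameters between the two groups will be compared using" Student's t "tests for normally distributed data and the Mann-Whitney" U test otherwise. No time-to-event or competing-event method is named.
- **Analysis set and missing data.** The same section says that "the intention-to-treat analysis will only include participants with an informed consent", and adds: "If missing data are more than 5 %, multiple imputations will be performed". Neither sentence mentions death.
- **Death.** It appears in the Background and under Safety ("Serious adverse events (SAE) are defined as death, a life-threatening injury or an extension of the length of hospital stay"). Mortality is not a listed outcome.

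**The concern.** Shorter is declared better, yet death also ends ventilation and ends a stay. A two-sample test on raw durations ranks a patient who dies on day 3 ahead of one who is weaned alive on day 10. If training improved early survival, it could appear to prolong ventilation and stay; if it worsened early survival, it could appear to speed recovery. Three secondary hypotheses are exposed, and mortality is not listed as an outcome that a reader could set beside them.

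The alternative is no safer. If patients who die before consenting are left out, the arms are compared among survivors, and who survives may itself depend on the allocation.

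**Working it through.** **Arm size.** The only figure that the plan computes is for the 6-Minute Walk Test: n = 2 × (1.960 + 0.842)² × 81² / 54² = 2 × 7.85 × 2.25 = 35.3, rounded up to 36 per group, as stated. Adding 14 gives 50 per group, and 2 × 50 + 15 = 115. I use 50 per arm. The article gives no figure for mortality, time of death, ventilation time or stay, so everything below is assumed.

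**Ventilation time.** Liberation is log-normal with median 8 days and log-SD 0.6 in both arms, so training has no effect on it. Time of death is log-normal with log-SD 0.5 and a varied median. Deaths enter at their observed duration in one of two ways:
- (a) Among patients assigned to die, the duration is the earlier of death and liberation.
- (b) Every patient assigned to die dies on the ventilator, so the time of death replaces the liberation time.

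The difference is the median in the lower-mortality arm minus that in the higher-mortality arm. The percentage is two-sided Mann-Whitney rejection (nominal 5%). Ranges cover repeated runs of 2,000 to 6,000 simulated trials.

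| Mortality | Median time of death | (a) | (b) |
|---|---|---|---|
| 30% vs 15% | 4 days | +0.9 day, 14–15% | +0.8 day, 12–13% |
| 30% vs 15% | 6 days | +0.6 day, 9% | +0.4 day, 6–7% |
| 30% vs 15% | 8 days | +0.4 day, 7% | 0.0 day, 5–6% |
| 30% vs 15% | 12 days | +0.2 day, 6% | −0.6 day, 8% |
| 30% vs 20% | 4 days | +0.6 day, 9–11% | +0.5 day, 7–8% |
| 20% vs 20% | 4 days | 0.0 day, 5% | 0.0 day, 4–5% |

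The distortion is largest when deaths come well before typical liberation. It fades as they come later and, under (b), changes sign when deaths come after it. With equal mortality and timing there is none.

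**Length of stay.** Stay is log-normal with median 14 days and log-SD 0.7, deaths are uniform on days 3 to 10, and training has no effect on stay (4,000 trials). The table gives the rate of a significantly shorter stay in the arm with more deaths (nominal 2.5% in that direction).

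| Mortality | Mann-Whitney | t test | Difference in medians |
|---|---|---|---|
| 20% vs 20% | 2.5% | 2.5% | 0.0 day |
| 20% vs 30% | 8.8% | 6.8% | −1.4 days |
| 20% vs 40% | 25.1% | 15.5% | −2.5 days |
| 10% vs 20% | 8.4% | 6.2% | −1.4 days |
| 10% vs 30% | 25.8% | 15.5% | −2.9 days |

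Ranking deaths as the worst outcome cuts the false benefit to 0.4% or less in every row with unequal mortality.

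**Ventilator-free days.** In the ventilation model, scoring every patient assigned to die as 0 over 28 days favours the lower-mortality arm by 1.8 days (30% vs 20%) and 2.8 days (30% vs 15%). The comparison rejects in 13–14% and about 25% of trials, although liberation is identical in the two arms. That signal comes from mortality alone.

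**The case against.** **The article does not say that deaths are counted at face value.** A reader might infer that a day-3 death will enter as a short, favourable duration and that the three hypotheses will therefore point the wrong way. The text does not support that much. The main analysis is limited to participants with informed consent, and under Recruitment, randomisation and blinding patients give their own written consent only after regaining judgement. A patient who dies ventilated never does. The proxy's presumed consent within 72 h may suffice, but the article does not say so. This stands: the inclusion of deaths at observed duration is an assumption. It does not clear the plan, because the other reading leaves a survivor comparison.

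**This is detail for an analysis plan that is not shown.** That holds in part, since the test sentence is generic and the outcome list only promises to report these durations. But the article itself fixes the direction of benefit, the raw measure and the test family. A plan that followed it would carry the problem forward.

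**The size depends on chosen inputs.** This stands. The 14% needs mortality to be halved and deaths to come at half the typical liberation time. The assumed distribution also puts Φ(ln(3/4)/0.5) = 28% of times of death before 72 h, in patients enrolled because at least 72 h of ventilation was expected.

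**Ventilator-free days are not a neutral replacement.** This stands too. They answer a different question from the stated hypothesis and are driven largely by mortality.

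**Conclusion.** The concern holds in a conditional form. The plan treats shorter durations as benefit and names tests that cannot separate early death from early recovery, with no rule for death. Whether this misleads depends on two things that the article does not settle: how deaths enter the analysis, and whether mortality or its timing differs between the arms.

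For ventilation time, the unfavourable scenario gives about 0.9 day and roughly 14% rejection, falling to about 6 to 7% under model (a) when deaths come at a median of 8 to 12 days. For stay, false-benefit rates of about 8 to 26% arise when mortality differs by 10 to 20 percentage points and deaths fall early. These are illustrations, not predictions for this trial.

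The outcomes are secondary. The primary endpoints and the sample size are not affected by this point. It should be corrected, but it does not threaten the main conclusion.

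**What to change.** 1. Analyse time to liberation from ventilation alive, time to ICU discharge alive and time to hospital discharge alive, each with death as a competing event, and show cumulative incidence by arm.
2. State that all deaths in the analysis set are included, and whether a proxy's consent keeps in that set a patient who died before personal consent was possible. State also that a duration ended by death is not a missing value for multiple imputation.
3. Report mortality by arm beside these outcomes. Cumulative incidence of discharge alive also responds to mortality, though extra deaths now lower it and no longer look like benefit.
4. Keep raw durations as descriptive summaries, split by survival status.
5. Ventilator-free days may be added as a supplementary composite, labelled as partly a mortality effect.

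The cost is modest extra analysis work. The estimand also changes: the result becomes a rate of liberation or discharge alive, not a difference in days. Durations and serious adverse events, including death, are already collected. Table 1 schedules adverse events under the daily ICU stay only, so confirm that dates of death on the ward are captured. Trial status puts the end of recruitment at February 2016, so make the change before the data are compared by arm.

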### Recruitment, randomisation and blinding

Patients will be screened daily after their ICU admission for study eligibility by the physiotherapist and research nurse in charge and will be included after consultation with the responsible clinician. Reasons for nonrecruitment will be noted in a daily screening log. If a patient is considered eligible a nonparticipating doctor will reexamine the inclusion and exclusion criteria in order to safeguard the patients’ interests according to Swiss law on nonresponsive patients. Participants will then be randomised at a 1:1 ratio to either the experimental or control group by the responsible research nurse using sequentially numbered, opaque, sealed envelopes to ensure a concealed allocation [43]. The allocation sequence was generated in advance by a study nurse using unrestrictive computer-generated randomisation. Furthermore, according to the recommendations of Good Clinical Practice (GCP) the willingness to participate will be obtained in the form of a presumed consent from the patients’ proxy within 72 h (Table 1). After regaining the power of judgement, patients will be informed of the study in writing and asked retrospectively by a GCP-trained physician to provide written informed consent. Participants have the right to withdraw from the trial at any given time. If unwilling to participate or withdrawing from the trial, patients will be excluded from the study and asked if the data that has already been collected may be retained. The sample size will be adjusted for dropouts.

Due to the nature of the intervention it is not possible to maintain blinding for the treating physiotherapists, ICU staff or participants. However, the group of physiotherapists who will assess the main outcomes will be distinct from the treating therapists and will, therefore, be blinded to group allocation.

### Sample size

For patients with chronic obstructive lung disease the minimal clinically important difference for the 6MWT has been validated at 54 m [44]. Using this threshold and a mean walking distance of 301 m (SD 81) [45] a sample size calculation based on a statistical power of 80 % and an *α*-level of 0.05 requires a sample size of 36 participants per group, i.e. a total of 72 patients for the study. We expect a high correlation between the two primary outcomes and, therefore, only moderately corrected the size upwards by 14 patients each. We assume a dropout rate of 15 % and adjusted the sample size by 15, resulting in a total number of 115 patients. However, we obtained the approval of the Ethics Committee to recruit more patients, if needed, to compensate for a higher number of dropouts (denied informed consent).

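### Two unranked primary outcomes share one 0.05 level with no success rule; the 14 extra patients per group add power but do not control the type I error

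*Protocol article*

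**What the plan says.** The Outcome section names two primary measures at the same time point: "The primary outcome measures are functional capacity using the 6-Minute Walk Test (6MWT") and "the ability to perform activities of daily living using the Functional Independence Measure (FIM"). The Abstract and the Discussion repeat the pair, and neither outcome is ranked above the other.

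The Sample size section starts from the 6MWT alone. With a 54 m difference, an SD of 81 m and 80% power, "an *α*-level of 0.05 requires a sample size of 36 participants per group". It then turns to the second outcome: "We expect a high correlation between the two primary outcomes and, therefore, only moderately corrected the size upwards by 14 patients each". That gives 50 per group, and 15 more patients for dropout bring the total to 115.

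The Statistical analysis section gives one level for the group comparisons: "The level of significance will be set at *p* < 0.05". The Abstract gives the same level. Neither place mentions a split, an order of testing or a rule for a split result.

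The primary hypothesis links the outcomes. Trained patients are expected to "have an improved functional capacity and are, therefore, more functionally independent at hospital discharge".

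**The concern.** The sample size section treats two primary outcomes as a design problem and answers it with patients. Whether that is the right answer depends on what counts as success, which the article does not fix.

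- **Either outcome suffices.** The problem is type I error. Two chances at 0.05 give more than a 5% chance of a false primary claim, whatever the sample size.
- **Both must succeed.** The problem is power. Extra patients are then the right kind of remedy, but their number can be justified only with an assumed FIM effect, and none is given.

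At stake is what the trial may conclude. If one outcome gives a p-value between 0.025 and 0.05 and the other is not significant, the result could be reported as positive at 5% or as failing the primary hypothesis, and the article would support both. The Discussion foresees routine use and guideline development if superiority is shown, so the reading should not be chosen after the results are known.

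**Working it through.** **Inputs from the article.** Difference 54 m, SD 81 m, power 80%, alpha 0.05, allocation 1:1, 14 added per group, 15 added for dropout. The article does not state sidedness; two-sided is used because it reproduces the stated size. It gives no figure for the correlation, so values from 0 to 0.95 are assumptions.

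**1. The plan's own figure.** Per group, n = 2 × (1.960 + 0.842)² × (81/54)² = 35.3, rounded up to 36. This matches. (A one-sided test would need 28.) The total is 2 × (36 + 14) + 15 = 115, which also matches. No formula is given for the 14, so it can be added but not derived.

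**2. Either outcome suffices, each tested at two-sided 0.05.** With both null hypotheses true and jointly normal test statistics Z₁ and Z₂, the familywise error is P(|Z₁| > 1.96 or |Z₂| > 1.96). At zero correlation it is 1 − 0.95² = 0.0975. At other correlations it is one minus the bivariate normal probability of the square from −1.96 to 1.96:

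| Assumed correlation | Familywise error |
|---|---|
| 0 | 9.75% |
| 0.5 | 9.1% |
| 0.7 | 8.3% |
| 0.8 | 7.8% |
| 0.9 | 7.0% |
| 0.95 | 6.5% |

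The number of patients does not enter this calculation. Moving from 36 to 50 per group leaves every row unchanged.

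**3. Both must succeed, each tested at 0.05.** A false claim requires significance on both, including on an outcome with no true effect, so its probability cannot exceed 0.05. What remains is power. For the 6MWT at 50 per group, the expected test statistic is (54/81) × √(50/2) = 3.33, and the normal approximation gives power Φ(3.33 − 1.96) = 0.915 (noncentral t: 0.910). Power to win on both needs a FIM effect. If, as an assumption only, the FIM had the same standardised effect, joint power would be 0.915² = 0.84 at zero correlation, 0.87 at 0.7 and 0.89 at 0.9. The article gives nothing from which to check that assumption.

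**4. Cost of splitting alpha.** At 0.025 per outcome, n = 2 × (2.241 + 0.842)² × (81/54)² = 42.8, so 43 per group. The t-test needs slightly more: power is 0.799 with 44 and 0.809 with 45. With 50 analysable 6MWT results per group, noncentral t power at 0.025 is 0.853. The corresponding FIM figure cannot be computed.

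**The case against.** The strongest defence is that the article can be read consistently as requiring both outcomes. The primary hypothesis joins them, more patients are the proper remedy for that design, and high correlation properly reduces how many are needed. The 84% to 89% joint power in step 3 fits such a design. This stands as a possible reading and makes the inflation conditional. It does not settle the matter: the hypothesis describes an expected causal chain and is not a decision rule, and the fit depends on an assumed FIM effect.

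A second defence is that a full protocol or analysis plan may hold the rule, since the choice of procedure is often left there. Silence alone would indeed be no finding. Here, however, the article publishes both the significance level and its response to two primary outcomes, and under an either-outcome rule that response does not keep the error at the stated level.

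Two stronger readings are tempting and are not supported. A reader might infer that the trial's error rate is nearly double 5%. That needs an either-outcome rule, which the article does not state, and near-zero correlation, when it expects a high one. At 0.7 to 0.9 the ratio is about 1.4 to 1.7. A reader might also infer that the added patients already pay for a full alpha split. That is shown for the 6MWT only.

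**Conclusion.** The point holds in conditional form. The article fixes one 0.05 level and two unranked primary outcomes, fixes no success rule, and uses a remedy that acts on power alone.

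- **Either-outcome rule:** the error is above the stated 5% at every correlation examined. The figures rest on two-sided tests and jointly normal statistics, and the correlations are assumed.
- **Both-outcomes rule:** there is no excess error. The stated 80% power describes the 6MWT at 36 per group, and power for the joint claim is not established.

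Under both readings a split result has no pre-set interpretation. The sample size arithmetic for the 6MWT is correct and is not in question.

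**What to change.** State the success rule, dated before the outcome data are analysed, and choose one of two forms.

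1. **Either outcome may succeed.** Name a single procedure. With Holm, the smaller p-value must be at most 0.025, after which the other is tested at 0.05. Hochberg is an alternative, but the two differ when both p-values lie between 0.025 and 0.05, so the choice cannot stay open. Add to the Sample size section that 50 analysable patients per group give about 85% power for the 6MWT at alpha 0.025, and that power for the FIM has not been established.
2. **Both must succeed.** Test each at 0.05, say that both are required, and restate the 80% power as applying to the 6MWT alone.

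In either form, the expected correlation should not be offered as the reason that no alpha rule is needed.

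The cost is about one sentence in each of the two sections, with no added patients. The price is a stricter threshold for a lone significant outcome under the first form, or giving up a claim based on one outcome under the second.

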## Methods and design

We will conduct a prospective, single-centre, allocation-concealed and assessor-blinded randomised controlled trial with superiority design and 6-month follow-up. The study has been approved by the Ethics Committee of Canton Bern (KEK), Switzerland and is registered in the German Clinical Trials Register (DRKS00004347). This trial adheres to the recommendations from the Consolidated Standards of Reporting Trials (CONSORT) statement [31] (Fig. 1) and is conducted according to Swiss law and Good Clinical Practice (GCP) guidelines.

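### The 15% dropout allowance is miscalculated (115 leaves 97 to 98 patients, not 100) and is tied to denied consent, with nothing set aside for death before discharge or a missing walk test

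*Protocol article*

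**What the plan says.** The Sample size section of the protocol article builds the total in three steps.

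1. For the walk test it takes a difference of 54 m ("the minimal clinically important difference for the 6MWT has been validated at 54 m"), "a mean walking distance of 301 m (SD 81") and "a statistical power of 80"%. At an alpha of 0.05 this "requires a sample size of 36 participants per group, i.e. a total of 72 patients for the study".
2. It adds 14 patients per group because there are two primary outcomes that are expected to correlate highly. This gives 100.
3. It assumes 15% dropout and "adjusted the sample size by 15, resulting in a total number of 115 patients". The Abstract repeats 115 with 15 expected dropouts.

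The next sentence of that section reports ethics approval to recruit more "to compensate for a higher number of dropouts (denied informed consent"). The Statistical analysis section restricts the intention-to-treat set to participants with informed consent and says that the sample size calculation has adjusted for this. Under Outcome, both primary endpoints are measured at hospital discharge. Under Statistical analysis, missing data above 5% are to be multiply imputed.

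**The concern.** There are two separate problems.

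The first is arithmetic. A dropout rate is a fraction of those enrolled, so the number needed to finish is divided by one minus the rate. The article multiplies by one plus the rate instead. The 15% rate and the count of 15 cannot both describe 115 enrolled patients.

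The second is what the allowance covers. Read together, the Sample size and Statistical analysis sections assign it to denied consent. A patient can consent, or have consent given, and still have no walking distance at hospital discharge. The article itself points to such losses. Its section on ICU-acquired weakness cites raised ICU and hospital mortality and reduced walking ability. Its Study population section excludes only patients whose admission diagnosis rules out walking, so those who later become too weak to walk stay in the trial. The walk-test calculation nevertheless treats every retained patient as supplying a distance.

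At stake is how a null result on the walk test would be read: the number of patients with a measured distance may be well below the 100 that the calculation implies.

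**Working it through.** **Inputs.** Difference 54 m, SD 81 m, power 80%, alpha 0.05, 15% dropout and 14 extra per group come from Sample size. The 1:1 allocation comes from Recruitment, randomisation and blinding. A two-sided test is assumed because sidedness is not stated; a one-sided test would give 28 per group, so the article's 36 fits two-sided.

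**Reproducing the walk-test size.** The standardised effect is 54/81 = 0.667. By the normal approximation, n per group = 2 × (1.960 + 0.842)² × (81/54)² = 35.3, which rounds up to 36, so 72 in total. This matches the article. With the t distribution, 36 per group has 79.7% power and 36.3 per group are needed, a negligible difference.

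**Reproducing the total.** 2 × (36 + 14) = 100, and 100 × 1.15 = 115. This matches the article and shows how the 15 was obtained.

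**Correct inflation.**
- 100 / 0.85 = 117.6, so 118.
- 115 × 0.85 = 97.75, so 97 to 98 patients are retained.
- 15 / 115 = 13.0%.

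**Effect of the slip alone.** For 54 m (SD 81), two-sided t test at alpha 0.05, power is 91.0% with 100 patients and 90.4% with 97.75.

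**Effect of losses outside the allowance.** The article gives no rate for death before discharge or for no walk test, so the further loss f below is an assumption. Patients measured = 115 × 0.85 × (1 − f). Power is from the noncentral t. The alpha 0.025 column is also an assumption: it shows an equal split over the two primary outcomes, which the article does not specify.

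| Further loss f | Patients measured | Power, alpha 0.05 | Power, alpha 0.025 |
|---|---|---|---|
| 0% | 97.75 | 90% | 84% |
| 10% | 88 | 87% | 80% |
| 20% | 78 | 83% | 74% |
| 30% | 68 | 78% | 68% |
| 40% | 59 | 71% | 60% |

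**Where power crosses 80%.** At alpha 0.05, 2 × 36.3 = 72.6 patients are needed, so f = 1 − 72.6/97.75 = 26%. Using whole patients (37 per group, 74 in total), f = 1 − 74/97.75 = 24%. Hence roughly a quarter. At alpha 0.025, 2 × 44.05 = 88.1 patients are needed, so f = 1 − 88.1/97.75 = 10% (12% by the normal approximation, with 43 per group).

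**The case against.** The case for leaving the section alone has real weight.

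- **The slip is three patients.** That is 118 against 115, and it costs less than one percentage point of walk-test power. The Abstract's pairing of 115 with 15 dropouts does leave 100; only the 15% label is wrong. This stands, and the arithmetic part is minor.
- **More patients may be recruited.** Ethics approval exists, and the recruitment section says the sample size will be adjusted for dropouts. This answers a consent shortfall. As worded, the approval is for denied consent, so it does not clearly cover deaths or missing tests.
- **The sentence stating 15% names no cause.** That is true, and the recruitment section also mentions withdrawals. But the parenthesis about extra recruitment and the statement on the intention-to-treat set both point to consent, and no other cause is budgeted anywhere in the article.
- **There is slack.** The 80% belongs to 72 patients, so the 28 added patients act as a reserve for the walk test taken alone at alpha 0.05. This is correct, and it is why power stays above 80% until about a quarter more are lost. However, the article added those 28 for the second primary outcome; counting them as attrition reserve uses them twice.
- **Multiple imputation is planned.** It does not restore the information lost with an unmeasured distance, and a patient who has died has no walking distance to impute.

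A reader might infer more: that the stated power holds only if every consenting patient survives and walks. The documents do not support this, since power is still about 87% after a further 10% loss and 83% after 20% at the stated alpha. A reader might also score non-walkers as 0 m, inflate the SD and obtain far lower power. The article contains no such rule, and it names the Mann-Whitney test for non-normal data, so a t-test calculation on that mixture would not describe the planned analysis.

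**Conclusion.** The point holds in two parts. The dropout figure is wrong as written: 15% of 115 leaves 97 to 98 patients, and 115 in fact allows for 13%. Its effect on power is negligible. The allowance is also linked to denied consent and omits two foreseeable losses in ventilated ICU patients, death before hospital discharge and absence of a walk test.

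How much the omission matters depends on a rate that the article does not give. At the stated alpha of 0.05, further losses of 10 to 40% put walk-test power between about 87% and 71%, and the stated 80% is lost beyond roughly a 25% further loss. If alpha were split to 0.025, that threshold would be about 10%. These figures assume a two-sided t test, a 54 m difference, an SD of 81 m among those measured, equal groups and 15% consent loss first. They do not show that the trial is underpowered, only that the allowance does not cover what it would need to cover for the planned 100 to be analysed.

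**What to change.** Three changes of text, none of which adds patients:

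1. Correct the figure. State either that 115 allows for 13% denied consent, leaving 100, or that 15% denied consent leaves 97 to 98.
2. Count death before hospital discharge and no walk test at discharge as losses in their own right, separate from denied consent.
3. Restate walk-test power for 54 m (SD 81) over a stated range of such losses, for example the 10 to 40% tabulated above, at the alpha actually used for the two primary outcomes.

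The cost is a less favourable power statement.
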